### 9.3 Annual safety report

In addition to the expedited reporting of SUSARs, the sponsor will submit, once a year throughout the clinical trial, a safety report to the accredited METC, competent authority, and competent authorities of the concerned Member States.

This safety report consists of:

- a list of all suspected (unexpected or expected) serious adverse reactions, along with an aggregated summary table of all reported serious adverse reactions, ordered by organ system, per study;
- report concerning the safety of the subjects, consisting of a complete safety analysis and an evaluation of the balance between the efficacy and the harmfulness of the medicine under investigation.

#### 9.4 Follow-up of adverse events

All AEs will be followed until they have abated, or until a stable situation has been reached. Depending on the event, follow up may require additional tests or medical procedures as indicated, and/or referral to the general physician or a medical specialist.

SAEs need to be reported till end of study within the Netherlands, as defined in the protocol

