**Nature and extent of the burden and risks associated with participation, benefit and group relatedness:** A physical examination, electrocardiography and blood sampling will be performed in all participants. All subjects will be treated with eplerenone (50 mg twice daily) and placebo. Potential side effects of eplerenone include nausea, diarrhoea, constipation, hypotension, myalgia, and hyperkalemia. The chance for these side-effects to occur is limited, because the study is restricted to young healthy males with a normal renal function, and the duration of treatment will be only 8 days. We will

reduce the risk of hyperkalemia by excluding volunteers with an estimated MDRD  $<60$  mL/min/1.73 m^2 and a serum potassium  $\geq 4.8$  mmol/L. We will monitor serum potassium in the first week after start of study medication. Blood will be drawn 6 times during the study and 1 time before randomization. Volunteers will visit our clinic 9 times in total. On the four experimental days, a 27 gauge needle (outer diameter 0.4 mm) will be inserted into the brachial artery for local drug administration. This can cause a haematoma. The administration of dipyridamole, caffeine, adenosine and sodium-nitroprusside into the brachial artery has been performed many times previously by our study group, and is considered to be safe. There is no direct benefit for the participants from this study.

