On the 7th day of treatment, the vasodilator response to intra-arterial administration of 3 increasing dosages of dipyridamole (10, 30 and 100 ug/min/dL per forearm) will be evaluated, in the absence and presence of intra-arterial infusion of caffeine (90 ug/min per 100 mL of forearm volume). In addition, PORH to 2 incremental periods of forearm ischemia (2 and 5 minutes) will be measured. Forearm ischemia will be induced by inflation of an upper arm cuff to 200 mmHg. During a separate visit (day 8), the vasodilator responses to intra-arterially infused sodium nitroprusside (60 and 600 ng/min/dL) and adenosine (1.5 and 5.0 ug/min/dL) will be determined, to exclude non-specific effects of eplerenone on vascular reactivity and adenosine sensitivity.

Treatment duration of 8 days means administration of eplerenone or placebo twice daily during 7 days and once daily on day 8.

After this first experiment, a wash out period of 4 weeks will avoid any carry-over effect of eplerenone. After these 4 weeks, the participant will be crossed over to receive the alternative treatment arm during 8 days. Again, we will monitor serum on day 3, 4 or 5, and on day 7 and 8 exactly the same experiments will be performed.

The subjects will be studied in supine position after an overnight fast and at least 24 h of caffeine and alcohol abstinence (since caffeine is an adenosine receptor antagonist and alcohol can also affect the adenosine metabolism). Experiments are performed in a temperature-controlled room (24 °C) in the morning after an overnight fast. At the start of the experiment, we will insert a venous cannula into the antecubital vein of the dominant arm for blood drawing. Blood will be drawn before start of each experiment: 20.5 mL on

day 7 for the determination of the serum potassium, sodium, creatinine, plasma caffeine (to check compliance with caffeine abstinence), aldosterone, renin, and eplerenone concentration; and 3 mL on day 8 for the determination of plasma caffeine only. Subjects with a circulating caffeine concentration > 1.0 mg/l will be excluded from analyses. Twenty-four hours urine samples will be collected and sodium and creatinine will be determined, to ensure that salt intake is approximately the same during both treatment days.

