Study medication will be taken under supervision of the researcher. One hour after ingestion of the drug, a 27-gauge needle (B. Braun Medical B.V.) will be inserted into the brachial artery of the non-dominant arm for intra-arterial drug administration. The outer diameter of this needle is 0.4 mm. In both arms, forearm blood flow (FBF) will be measured simultaneously with venous occlusion plethysmography, using mercury-in-silastic-strain gauges and occluded hand circulation as described previously. (12) Thirty minutes after cannulation of the brachial artery, normal saline is infused with concomitant measurement of baseline FBF for 5 min.

So, approximately 1.5 hours after ingestion of the study medication, the experiment will be started and FBF will be measured around the  $T_{\max}$  of eplerenone (approximately 2 hours) Three experiments will be performed, which are all separated by 30 minutes of wash-out.

1. FBF will be measured during the administration of increasing dosages of dipyridamole into the brachial artery. These dosages are similar to a previous study of our group. (10) We hypothesize that in patients treated with eplerenone, the dipyridamole-induced vasodilation is potentiated due to upregulation of CD73.
2. Subsequently, we will measure the vasodilator response to 2 incremental periods of arterial occlusion ('post-occlusive reactive hyperemia'). Forearm ischemia will be induced by inflation of an upper arm cuff to 200 mmHg, as described previously. (11) We have previously demonstrated that the PORH after 2 and 5 minutes of ischemia is potentiated by statins (by increasing the extracellular formation of adenosine) (11) and by dipyridamole (by inhibition of the ENT transporter). (12)

3. We will finish the experiment on day 7 with measurement of FBF during the concomitant administration of the three increasing dosages of dipyridamole and of caffeine (90 ug/min per 100 mL of forearm volume) into the brachial artery.
4. Finally, on day 8, we will record the forearm vasodilator response to the administration of adenosine (1.5 and 5.0 ug/min/dL) and SNP (60 and 600 ng/min/dL) to exclude non-specific effects of eplerenone on vascular function and adenosine sensitivity.

Furthermore, we will measure blood pressure at baseline and during the experiments, on day 7 and 8, in all volunteers.

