### 12.5 End of study report

The sponsor will notify the accredited METC and the competent authority of the end of the study within a period of 90 days. The end of the study is defined as the last patient's last visit.

In case the study is ended prematurely, the sponsor will notify the accredited METC and the competent authority within 15 days, including the reasons for the premature termination.

Within one year after the end of the study, the investigator/sponsor will submit a final study report with the results of the study, including any publications/abstracts of the study, to the accredited METC and the Competent Authority.

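### SAE reporting ends at the last participant's last visit, and the last visit described is itself a dosing and arterial-cannulation day, so no SAE collection after final exposure is described for the last man to finish

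*Protocol*

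**What the plan says.** Section 9.4 of the protocol: "SAEs need to be reported till end of study within the Netherlands, as defined in the protocol". Section 12.5 supplies the definition: "The end of the study is defined as the last patient's last visit".

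The schedule in section 3 ends with the second treatment period: "Again, we will monitor serum on day 3, 4 or 5, and on day 7 and 8 exactly the same experiments will be performed". Day 8 is still a treatment day: "Treatment duration of 8 days means administration of eplerenone or placebo twice daily during 7 days and once daily on day 8". Section 3 has the capsule taken under supervision before the artery is punctured. The Summary confirms that day 8 includes the puncture: "On the four experimental days, a 27 gauge needle (outer diameter 0.4 mm) will be inserted into the brachial artery for local drug administration". Four experimental days means days 7 and 8 of each of the two periods. Section 3 then describes the infusions: "Finally, on day 8, we will record the forearm vasodilator response to the administration of adenosine", together with sodium nitroprusside.

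On the number of contacts, the Summary says: "Volunteers will visit our clinic 9 times in total". It also gives 6 blood draws during the study and 1 before randomisation.

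**The concern.** The SAE cut-off is tied to a date shared by the whole trial, not to each man's own exposure. For the last man to finish, that date appears to be the day of his last capsule, his fourth arterial puncture and his last infusions. A serious event that begins the next day, for example a complication at the puncture site or a recognised serious effect of eplerenone, would lie outside the reporting rule as written. For the other men the reporting time after final exposure is set by how far apart participants happen to be recruited, which has nothing to do with safety. What is at stake is whether serious events after the last visit are captured at all. The primary efficacy analysis is not affected.

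**Working it through.** There is no power or error-rate figure to reproduce. The check is a count of the schedule, followed by a reading of each rule that might cover the gap.

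**Blood draws.** In each period blood is drawn on day 3, 4 or 5, on day 7 and on day 8 (section 3). Two periods × 3 draws = 6, which matches the Summary. Adding the pre-randomisation draw gives 7 in total. Every stated draw is therefore accounted for by day 8 of period 2, and none is left for a later visit.

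**Visits.** Screening plus 3 visits in each period gives 1 + 2 × 3 = 7 described visits, against 9 stated. Two are unexplained. One extra visit at the start of each period would give 1 + 2 × 4 = 9, but the protocol does not say that this is what they are.

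**Length of the reporting window.** Let D_i be the date of participant i's day 8 in period 2. If no contact follows day 8, the end of study is E = max(D_i), and participant i's window after final exposure is W_i = E − D_i.

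- Last man to finish: D_i = E, so W_i = 0 days. This needs no assumption about recruitment.
- Every other man: W_i is the gap between his day 8 and the last man's. The protocol gives no recruitment rate, so W_i cannot be computed.
- If an undescribed visit took place d days after day 8, then E = max(D_i) + d. The last man's window would be d and every man would have at least d. The protocol states no such visit and no such d.

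**Other rules that might fill the gap.**

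- Following AEs until they abate or stabilise (9.4) concerns events already recorded. Section 9.2.1 defines AEs as occurring during the study, so a new event after the cut-off does not enter.
- The SUSAR rule (9.2.3) has no end date. It requires an event that is serious, suspected to be a reaction to the product under investigation, and unexpected against the product information. Section 6.4 lists hyperkalaemia, hypotension and myocardial infarction as known effects of eplerenone, so these would probably count as expected. A puncture complication is not a reaction to the investigational product.
- Repeat potassium draws after treatment (8.6) apply only to men excluded for a raised value, and the exit interview only to men who withdraw.
- The day 8 blood sample is for caffeine only (section 3), so it gives no safety reading either.

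None of these captures a new expected serious reaction, or a new puncture complication, arising after the last visit in a man who completed the study.

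**The case against.** The strongest reply has four parts.

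1. The two unexplained visits could include one after day 8. That is possible. A visit without a blood draw fits the stated counts, and it would give every man some cover. The conclusion must therefore be worded as what the protocol describes, not as a certain 0 days. This part stands as a qualification.
2. The SUSAR rule has no end date, so a late drug reaction is not wholly outside reporting. This is correct for unexpected serious reactions that reach the sponsor. It leaves out expected serious reactions and procedural complications, and no contact is described through which a late event would come to light.
3. Sections 9.4 and 12.5 do not conflict. That is correct: 9.4 defers to a definition and 12.5 supplies it. The problem is where the combined rule puts the cut-off.
4. The trial is small, the needle is fine (0.4 mm), treatment is short, and the stated half-life is 3–5 hours. This stands, and it limits the severity.

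A reader might also infer that unequal observation biases the safety comparison of eplerenone with placebo. The documents do not support this. Under equal allocation of the two sequences (an assumption), each treatment comes second in about 7 of the 14 men, so the shorter window falls on both alike. The protocol also has no comparative safety endpoint. Nor can the 4-week wash-out be read as a required safety window, because section 3 justifies it by carry-over. No count of men with short cover can be given, because the recruitment rate is not stated.

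**Conclusion.** The concern holds on the protocol's text, as a minor point. SAE reporting ends at a trial-level date. On the schedule described, that date is the last participant's final dosing and cannulation day. He then has no SAE reporting after that visit, and the time available to the other men depends only on recruitment timing.

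This rests on one assumption: that neither of the two undescribed visits comes after day 8 of period 2. If one does, everyone has some cover. The reporting period would still be fixed by a common calendar date, and its minimum would still not be stated. It would be too strong to say that all late drug reactions go unreported, or that the treatment comparison is biased. The gap concerns expected serious reactions and puncture complications, of which few are expected.

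**What to change.** In section 9.4, replace the trial-level cut-off with an SAE collection period for each participant, running to a fixed interval after his own last exposure to study drug or study procedure. The sponsor should set the length and state it. Close the period with one telephone contact for each man.

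In section 12.5, define the end of study as the last participant's last contact, so that it stays consistent with the revised 9.4. The same amendment should say what the two undescribed visits are.

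The cost is a few sentences, 14 short calls and an end of study later by the chosen interval. No procedure, treatment or clinic visit changes.

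Suggested wording for 9.4: *SAEs will be collected for each participant until [interval set by the sponsor] after his last exposure to study medication or study procedures; this period is closed by a telephone contact.*

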#### 9.5 [Data Safety Monitoring Board (DSMB) / Safety Committee]

Not applicable

## 10. Statistical analysis

### 10.1 Primary study parameter(s)

The FBF response to the administration of dipyridamole after treatment with eplerenone compared to placebo will be log transformed and evaluated using a linear mixed-model analysis with random factor subject, fixed factors dipyramole dose, eplerenone (versus placebo), dipyramole dose \* eplerenone, and period. The logarithm of the baseline FBFs will be included as co-variables. The results will be back-transformed and 95% confidence intervals will be presented. A two-sided p-value of  $< 0.05$  will be considered to be statistically significant.

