#### 4.4. Sample size calculation (performed by [name], dept. of Health Evidence)

Based on earlier, similar studies with a parallel groups design, we expect that the standard deviation of the logarithm of the FBF will be approx. 0.35 and that the correlations between the measurements within each period of the cross-over will be approx. 0.7. (12, 13) Based on these assumptions and a difference of 25% between the groups, the analysis described in the statistical section of the protocol, carried out on two parallel groups of 12 subjects, is expected to have approximately 80% power (two-sided testing at 0.05; the design factor for a pooled analysis on k follow-up measurements adjusted for baseline is  $\frac{1}{k} + k \cdot \frac{1}{k} \rho - \rho^2$ ). The proposed study is a cross-over trial, so the power of a 12-subject-study may be higher, as the subjects serve as their own control. However, this is to some extent also the case in a parallel study, because the baseline is included as a covariate in the analysis. Hence, the power of a cross over study with 12 evaluable subjects is expected to be only marginally higher than 80%. In order to have 12 evaluable subjects, we will enroll 14 subjects. (see also paragraph 8.5)

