### 10.2 Secondary study parameter(s)

The reduction in FBF response, due to the administration of caffeine in the presence of dipyridamole and eplerenone, will be analysed in a similar way, using a linear mixed-model analysis with random factor subject, fixed factors dipyramole dose, caffeine (yes/no), dipyramole dose \* caffeine, and period. The logarithm of the baseline FBF will be included as co-variables. The dependent variable will be the log-transformed FBF after eplerenone administration (with and without caffeine). Other endpoints will be analysed using similar random effects models. A p-value of  $< 0.05$  will be considered to be statistically significant.

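### The primary model in 10.1 has no visit-level random effect, so the pooled eplerenone contrast is tested against dose-to-dose error and its p-value is probably too small

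*Protocol*

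**What the plan says.** Section 10.1 writes out the primary model. Log FBF is "evaluated using a linear mixed-model analysis with random factor subject, fixed factors dipyramole dose, eplerenone (versus placebo"), and the fixed part is completed by "dipyramole dose \* eplerenone, and period". Baseline enters as follows: "The logarithm of the baseline FBFs will be included as co-variables". The test is two-sided at 0.05. No visit-level random term and no within-visit covariance is named in 10.1 or elsewhere in the protocol.

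The Summary defines the primary comparison as eplerenone against placebo pooled over the dipyridamole doses. Section 3 puts all three doses on day 7 of each treatment period, in one experimental session, and separates the periods by a four-week wash-out.

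Section 4.4 puts the SD of log FBF at about 0.35. On dependence it states: "the correlations between the measurements within each period of the cross-over will be approx. 0.7". It takes "a difference of 25% between the groups" and arrives at about 80% power for two parallel groups of 12. It expects the cross-over to do only slightly better.

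Section 10.2 writes out a caffeine model of the same form and adds: "Other endpoints will be analysed using similar random effects models".

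**The concern.** The unit that receives eplerenone or placebo is the period. Twelve evaluable subjects give 24 day-7 visits. The three FBF values of a visit share one cannulation, one set-up and one day, so whatever is particular to that visit shifts all three together.

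A subject intercept alone imposes one common correlation on all six values of a subject, whether two values come from the same morning or from visits about five weeks apart. If values within a visit are more alike than values across visits, the shared visit deviation goes into the residual and is counted as independent dose-level noise. The standard error of the pooled treatment effect is then too small and its degrees of freedom too many.

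This is a 12-subject mechanistic study whose conclusion rests on one p-value and one 95% confidence interval, so an understated standard error goes straight into the claim that eplerenone activates CD73. The eplerenone-versus-placebo comparisons covered by the last part of 10.2, such as post-occlusive reactive hyperaemia (PORH), would inherit the problem.

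**Working it through.** **1. Inputs.** From section 4.4: 12 evaluable subjects, SD of log FBF 0.35 (variance 0.1225), within-period correlation 0.7, difference 25% (ln 1.25 = 0.2231). From section 3: three doses per visit, two visits. From section 10.1: the fixed and random terms. Assumed, because the protocol does not give it: the between-visit correlation, written r and varied from 0 to 0.7.

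**2. The plan's own power.** The design factor is poorly legible in the text. Read as (1 + (k−1)ρ)/k − ρ² with k = 3 and ρ = 0.7, it is 2.4/3 − 0.49 = 0.31. The adjusted SD is 0.35 × √0.31 = 0.195 and the SE is 0.195 × √(2/12) = 0.0796. Then 0.2231/0.0796 = 2.80 and Φ(2.80 − 1.96) = 0.80. The stated 80% reproduces (76.5% with a t-test on 22 df), so the inputs are usable.

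**3. Mechanism by hand, leaving baseline out, at r = 0.35.**
- Visit variance: (0.7 − 0.35) × 0.1225 = 0.0429. Residual variance: 0.3 × 0.1225 = 0.0368.
- True SE of the pooled contrast: √[2 × (0.0429 + 0.0368/3)/12] = 0.096.
- The subject-only model pools two error strata. Subject-by-period has 12 − 2 = 10 df and expected mean square 0.0368 + 3 × 0.0429 = 0.165. Dose within visit has 48 − 4 = 44 df and expected mean square 0.0368. The pooled value is (10 × 0.165 + 44 × 0.0368)/54 = 0.0606.
- SE that the model reports: √[2 × 0.0606/36] = 0.058.
- The true SE is 0.096/0.058 = 1.65 times the reported one. A nominal critical value of 2.00 acts like 2.00/1.65 = 1.21, which is a two-sided error of about 23%. Simulation of this no-baseline case gave 23.7%.

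**4. Simulation of the written model with baseline, no drug effect.** REML with a random subject intercept and the fixed terms of 10.1. The pooled contrast is t-tested on residual df: 72 observations − 12 subjects − 7 = 53 with one baseline covariate. The visit-level analysis regresses each subject's difference in visit means on sequence and baseline difference, with 12 − 3 = 9 df. There were 5,000 trials per setting for the own-visit baseline and 3,000 when the subject-mean baseline was added, which models both visits' baselines.

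| r | 10.1 model, own-visit baseline | 10.1 model, both visits' baselines | Visit-level analysis (own-visit runs) |
|---|---|---|---|
| 0 | 19.1% | 18.8% | 5.2% |
| 0.35 | 17.2% | 16.7% | 5.2% |
| 0.5 | 15.6% | not run | 5.2% |
| 0.6 | 13.6% | 11.5% | 4.9% |
| 0.7 | 10.7% | 5.7% | 4.9% |

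Repeat runs with separate code moved single entries by up to about 2 percentage points (for example up to 15% at 0.6). With 14 subjects and the own-visit baseline the model gave 16.9% at r = 0.35 and 10.3% at 0.7. If the within-visit correlation is only 0.5, the figures are 16.3% at r = 0 and 9.0% at r = 0.5.

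**5. The row at r = 0.7.** Here the visit variance is zero, so a missing visit term costs nothing. Without any baseline covariate the written model gave 5.4%. The 10.7% arises because the baseline slope is driven largely by differences between subjects, while the baseline difference between a subject's two visits is pure noise in this setting. Adjusting for it adds the same error to all three doses of a visit. Entering both visits' baselines removes most of this.

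**6. Power after correction, at a 25% difference.** The visit-level analysis has about 66% at r = 0, 73% at r = 0.35 and 98% at r = 0.7.

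**The case against.** **The size is conditional.** The between-visit correlation is nowhere in the protocol, and section 4.4 draws on parallel-group studies, which cannot separate stable subject differences from visit-to-visit variation. A reader might infer a fixed false-positive rate of 10-19%. The document does not support that. The lower end comes from baseline handling, and with both visits' baselines entered (the plural in 10.1 permits this) the error falls to 5-6% as r nears 0.7. That favourable case, however, needs values about five weeks apart to correlate as strongly as values from one morning.

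**Full independence is not claimed.** A reader might say that the model counts the doses as unrelated replicates. It does not: the subject intercept correlates them, and they are independent only given the subject.

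**4.4 and 10.1 do not flatly contradict each other.** Section 4.4 says its calculation applies the planned analysis to parallel groups. There each subject has one visit, so a subject effect is also a visit effect and the subject-only model fits. The gap opens when the same random structure is carried to the cross-over.

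**The caffeine model is not affected in this way.** A reader might extend the criticism to all of 10.2. The caffeine comparison uses the eplerenone period only and is made within one visit. Each subject contributes one period, so subject-by-period cannot be separated from subject.

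**An analysis plan could refine this.** Residual covariance and the degrees-of-freedom method are often settled there, and 10.1 does not exclude a within-visit covariance. This limits confidence in any exact figure. But the random factor is stated, and an analysis that follows the text as written has the problem.

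**Conclusion.** The point holds in conditional form. As written, the 10.1 model uses the wrong error term for the pooled eplerenone contrast whenever values within a visit are more alike than values across visits. The type I error is then about 15-19% for between-visit correlations from 0 to 0.5 and 11-15% at 0.6. As that correlation approaches 0.7 it lies between 5-6% (both visits' baselines entered) and about 11% (own-visit baseline only).

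These figures assume 12 subjects with complete data, normal log FBF with SD 0.35, a common within-visit correlation of 0.7 that includes the baseline, and residual-df t-tests; z-tests gave similar results (10.5-19.8% with the own-visit baseline).

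The protocol gives indirect evidence on where in this range the trial sits. Section 4.4 expects cross-over power only slightly above 80%. Correctly analysed, power is 73% at r = 0.35 and 98% at r = 0.7, so that expectation corresponds to a correlation somewhere between them, where the written model (own-visit baseline) gives roughly 11-17%. This is an inference, not a stated input.

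**What to change.** - **Section 10.1:** add a random subject-by-period (visit) effect to the random subject effect, with Kenward-Roger or Satterthwaite degrees of freedom. Name the eplerenone contrast averaged over the three doses as the primary test. With all three doses present, analysing the 24 visit means of log FBF is equivalent. State whether the baseline covariate is the visit's own value or both visits' values.
- **Section 10.2:** apply the same structure to the models that compare eplerenone with placebo, such as PORH. Leave the caffeine model out of this change.
- **Section 4.4:** restate power for the corrected model over a stated range of between-visit correlation.

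The cost is a few sentences and no extra measurements. The downside is wider confidence intervals, and power that may fall below the stated 80% if the between-visit correlation is low. The sponsor should weigh that against the planned 12 evaluable subjects.

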## Summary

**Rationale:** Various studies have reported cardioprotective effects of mineralocorticoid receptor (MR) antagonists in the setting of an acute myocardial infarction. In a recent animal study, the protective effect of MR antagonists on infarct size was completely abolished in CD73 knock-out and adenosine A2b receptor knock-out mice, and by co-administration of adenosine receptor antagonists in rats. These findings suggest that extracellular formation of adenosine is crucial for this protective effect and that MR antagonists stimulate extracellular adenosine formation by the enzyme CD73.

**Objective:** To investigate whether eplerenone promotes adenosine receptor stimulation by activating CD73

**Study design:** Single center, randomized, double-blinded, placebo-controlled, cross over study

**Study population:** Twelve + 2 healthy male volunteers, aged 18-40 years

**Intervention (if applicable):** All subjects will be randomized to treatment with either eplerenone (50 mg twice daily) or a placebo. Duration of the treatment will be 8 days for both eplerenone, and placebo. After a 4-week-period the subjects will be crossed over to the other treatment group.

**Main study parameters:** A venous cannula will be inserted into the antecubital vein of the dominant arm for blood drawing. The brachial artery of the non-dominant arm will be cannulated for local drug administration. We will measure forearm blood flow (FBF) with venous occlusion plethysmography. Subsequently, the FBF response will be measured to 1) the administration of incremental dosages of dipyridamole; 2) increasing periods of arterial occlusion; 3) concomitant administration of dipyridamole and caffeine and 4) two different concentrations of both adenosine and sodium-nitroprusside.

**Primary analysis/endpoint:** FBF, pooled over the various dosages of dipyridamole, will be compared between eplerenone and placebo.

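### The baseline covariate in the primary model is measured on study drug, so if eplerenone shifts resting flow the adjusted contrast is neither the pooled FBF difference nor the response relative to rest

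*Protocol*

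**What the plan says.** Protocol section 10.1 analyses log FBF under dipyridamole in a linear mixed model. Subject is random; dose, treatment, their interaction and period are fixed. It then adds: "The logarithm of the baseline FBFs will be included as co-variables".

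Section 3 says how that baseline is obtained: "Thirty minutes after cannulation of the brachial artery, normal saline is infused with concomitant measurement of baseline FBF for 5 min". The study drug has been taken under supervision earlier that morning: "So, approximately 1.5 hours after ingestion of the study medication, the experiment will be started". The dipyridamole experiment falls on day 7 of treatment, and in the second period "on day 7 and 8 exactly the same experiments will be performed". The Summary counts four experimental days, which are days 7 and 8 of each period. No FBF measurement off study drug is described.

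The target is worded in two ways. The Summary gives a flow level: "FBF, pooled over the various dosages of dipyridamole, will be compared between eplerenone and placebo". The primary objective (section 2), hypothesis 1 (section 3) and the main endpoint (section 8.1.1) speak of the vasodilator or FBF response to dipyridamole.

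**The concern.** A covariate measured before treatment differs between treatments only by chance, and adjusting for it adds precision without changing what is estimated. A covariate measured on treatment does not have that guarantee. If eplerenone shifts resting flow, the adjusted treatment contrast equals the total effect on log FBF minus the covariate slope times the shift in log resting flow.

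The slope decides what the contrast means. A slope of 0 gives the difference in FBF level, which is the Summary's wording. A slope of 1 gives the change in response relative to rest, which is the natural reading of the objective and of section 8.1.1. A fitted slope in between gives neither.

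A resting shift is not far-fetched. The hypothesis is that eplerenone increases extracellular adenosine, and section 1 lists vasodilation among adenosine's effects. At stake is the reading of the result: part of a pure resting shift could be reported as an augmented response to dipyridamole.

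**Working it through.** **Inputs from the protocol.** SD of log FBF 0.35, within-period correlation 0.7, difference 25%, 12 evaluable subjects (all section 4.4); three dipyridamole doses, so k = 3 (section 3).

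**Assumed, because the protocol gives no value.** The between-period correlation (varied from 0 to 0.7) and the size of any resting-flow shift (+10% and +15% as illustrations).

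**1. The plan's own figure.** The formula in section 4.4 is broken in the text at hand; it is read here as 1/k + ((k-1)/k)ρ - ρ².
- Design factor: 1/3 + (2/3)(0.7) - 0.49 = 0.31.
- Adjusted SD: 0.35 × √0.31 = 0.195.
- SE with two groups of 12: 0.195 × √(2/12) = 0.0796.
- ln 1.25 / 0.0796 = 0.2231 / 0.0796 = 2.80.
- Power, normal approximation, two-sided 0.05: 80.1%, against the stated 80% or so. It reproduces.

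**2. Slope on log baseline.** The section 10.1 model was fitted by REML to simulated cross-over data with the SD and within-period correlation above.

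| Between-period correlation (assumed) | Fitted slope |
|---|---|
| 0 | 0.70 |
| 0.3 | 0.66 |
| 0.5 | 0.59 |
| 0.6 | 0.54 |
| 0.7 | 0.41 |

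So about 40-70% of any shift in log resting flow is taken out of the treatment contrast.

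**3. Resting flow +10%, FBF under dipyridamole +25%.** Adjusted log effect = ln 1.25 - slope × ln 1.10, with ln 1.25 = 0.2231 and ln 1.10 = 0.0953.
- Slope 0.70: 0.2231 - 0.0667 = 0.1564, ratio 1.17.
- Slope 0.59: 0.2231 - 0.0562 = 0.1669, ratio 1.18.
- Slope 0.41: 0.2231 - 0.0391 = 0.1841, ratio 1.20.

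The total ratio is 1.25. The response ratio is 1.25 / 1.10 = 1.14. The adjusted estimate lies between them.

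**4. Resting flow +15%, dilator ratio unchanged.** FBF under dipyridamole also rises 15%, and the true response ratio is 1. Apparent augmentation = exp((1 - slope) × ln 1.15) - 1, with ln 1.15 = 0.1398.
- Slope 0.70: exp(0.0419) - 1 = 4.3%.
- Slope 0.59: exp(0.0573) - 1 = 5.9%.
- Slope 0.41: exp(0.0825) - 1 = 8.6%.

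**5. Precision of a ratio contrast.** Take the mean of the three log FBFs minus log saline FBF in each period.
- Variance of the mean of three: (1 + 2 × 0.7)/3 = 0.8, in units of 0.35² = 0.1225.
- Variance of the difference from baseline: 0.8 + 1 - 2 × 0.7 = 0.4.
- Treatment difference over two periods: 2 × 0.4 = 0.80. This takes one common correlation between all measurements of different periods; those terms then cancel.
- SE = √(0.80 × 0.1225 / 12) = 0.0904.
- Power by noncentral t on 10 df: about 61% for a response ratio of 1.25 (0.2231 / 0.0904 = 2.47), and about 25% for 1.136 (0.1278 / 0.0904 = 1.41).

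**The case against.** The strongest reply is that the bias rests on a premise the protocol does not supply. It never says that eplerenone changes resting FBF. Section 6.5 expects no significant change in blood pressure. Section 1 describes rapid cellular uptake of adenosine, which dipyridamole is there to block, so the resting effect could be small. This stands: with no resting shift nothing is removed, and the +10% and +15% are illustrations.

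Second, most of the protocol names the response to dipyridamole as target. For that target, same-session pre-infusion flow is the natural reference, and removing resting differences is wanted. This also stands, and it rules out a tempting inference, that the adjustment biases the trial towards no effect. That is true only against the Summary's total FBF difference. Against the response ratio of 1.14 in the illustration, the adjusted 1.17-1.20 is too high. What the reply does not remove is that a slope of 0.4-0.7 takes out only part of the shift.

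Third, covariate adjustment is more precise than a ratio. This is a good reason to keep the adjusted model as primary.

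**Conclusion.** The point holds in conditional form. Every baseline FBF described is an on-treatment value. If eplerenone shifts resting flow, the section 10.1 contrast falls between the two targets that the protocol names. With the assumed shifts, the adjusted ratio is about 1.17-1.20 where the total is 1.25 and the response 1.14, or an apparent augmentation of about 4-9% (about 6% at between-period correlation 0.5) where the response is unchanged. These figures rest on the protocol's SD and within-period correlation and on assumed between-period correlations and resting shifts. If resting flow does not move, there is no bias.

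Two stronger readings are not supported. A reader might infer that the sample size is wrong because its design factor presumes a baseline that treatment cannot move. But the stated power reproduces, and planning without a resting shift is consistent with a protocol that posits none. A reader might also infer that the non-infused arm is wasted, since "In both arms, forearm blood flow (FBF) will be measured simultaneously with venous occlusion plethysmography" and section 10.1 gives it no explicit role. But section 10.1 refers to baseline values in the plural without listing them, and how the control arm enters is detail that a statistical analysis plan may settle.

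**What to change.** 1. Keep the adjusted model as the primary analysis.
2. State in section 10.1 that the baseline is the on-treatment, pre-infusion saline value and that the target is the response to dipyridamole. Align the Summary's wording of the primary endpoint with this.
3. Analyse day-7 saline FBF, eplerenone versus placebo, as a named outcome.
4. Report the treatment contrast in log(FBF/saline FBF) as a supportive analysis. If resting FBF differs between treatments, interpret any claim of an augmented vasodilator response in the light of this estimate.

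The cost is analysis work and a wording change; no new measurement, visit or subject is needed. The downside is precision: the ratio contrast has about 61% power for a 25% response difference and about 25% for a 14% difference. It should therefore support interpretation and not serve as a formal condition for success.
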